## Abstract

**Background:**

Different coping strategies have been associated with various effects on infertile couples’ mental health. Considering the close interaction between couples, the present study aims to develop coping strategies for infertile couples using a couple-based approach.

**Methods:**

The present mixed-methods study will be conducted in three phases. In order to develop coping strategies, a qualitative study will be conducted in the first phase, during which semi-structured interviews will be implemented with infertile couples in order to collect data related to their lived experiences in using coping strategies. These data will be inductively analyzed using qualitative content analysis and interpretative phenomenological analysis. In the second phase, using the Delphi method, an initial draft of coping strategies will be designed using a couple-based approach based on the data obtained from the qualitative study and the related literature review. In the third phase, the designed couple-based strategies will be provided to two groups of infertile couples as a randomized field superiority trial study. The couples’ levels of stress, anxiety, depression, and adjustment will be evaluated using validated questionnaires before and 3 months after the intervention.

**Discussion:**

Couple-based coping strategies encourage couples to become aware of each other’s feelings while interacting and choose a strategy based on such feelings.

**Trial registration:**

Iranian Registry of Clinical Trials IRCT20191014045102N1. Registered on 19 October 2021. Protocol version: Current protocol: version 1 (22 May 2022)

## Background

Infertility affects approximately 10 to 15% of couples of reproductive age worldwide [1, 2]. This experience is associated with a wide range of psychological problems for couples such as depression [3, 4], stress, anxiety [5, 6], low self-esteem [7, 8], and low psychological adjustment [9]. On the other hand, social pressures due to the infertility taboo can create a psychological imbalance between couples and, in some cases, weaken their relationships [10]. Domar et al. believe that infertility is a source of chronic stress and should be seriously taken into account as much as major physical health problems, such as cancer and coronary heart diseases [11]. Infertility is considered a crisis by most couples [12], and adaptive strategies under infertility stress are associated with adjustment and reducing the psychological burden of infertility [13].

Most couples choose coping strategies to deal with infertility and mitigate the resulting mental pressure. Coping strategies are a set of cognitive and behavioral efforts made to interpret, analyze, and modify a stressful situation [14]. Lazarus defines coping as a response to mental pressure such as infertility. Such a reaction is a personal attempt to overcome harmful, threatening, or challenging circumstances [15].

Coping strategies are classified into four groups: active coping, active avoidance, passive avoidance, and meaning-based coping [16]. The efficiency of any coping strategy depends on the controllable or uncontrollable conditions and social and cultural context of the society. For instance, some coping strategies to deal with maladjustment and psychological problems could affect inversely in various cultural environments [13]. Furthermore, couples’ close and comprehensive interactions can cause each spouse to be affected by their partner’s choice of coping strategies and psychological damage resulting from infertility. A coping strategy employed by each spouse could also influence their partner’s mental health [17].

However, the existing coping strategies are mainly focused on the individual. Coping strategies that can reduce an individual’s infertility stress may negatively impact the spouse’s mental health. Therefore, considering the interactive effect of couples’ coping strategies, it is essential to identify coping strategies whose interactive effect outcome is accompanied by a reduction in the psychological burden of infertility in both men and women, particularly in situations where men and women do not equally bear the psychological and social burden of infertility. In traditional societies where infertility is mainly attributed to women, they are more vulnerable to the social stigma of infertility than men [18].

Therefore, the present study intends to develop coping strategies for infertile couples using a couple-based approach and evaluate the effect of the designed coping strategies on infertile couples’ mental health. This trial will be a randomized field trial, superiority framework, with two parallel groups. The study objectives are as follows:Comparison of the depression, anxiety, and stress levels in the intervention and control before and after the interventionComparison of the infertility adjustment in the intervention and control before and after the intervention

## Methods

This mixed-methods sequential exploratory study will be conducted in three phases with the permission of the Ethics Committee of Isfahan University of Medical Sciences in Isfahan, Iran. This study will be conducted in three phases. The first stage will consist of data collection and preparation of lists of couple-based coping strategies and includes qualitative study and advanced literature review. The second stage will include the Delphi method and assess the feasibility of the designed coping strategies in a randomized field trial study.

### First phase: designing the couple-based coping strategies

The qualitative phase of the study will be conducted by inductive content and interpretative phenomenological analyses in order to explain the infertile couples’ lived experiences of using coping strategies. At this stage, to collect data, the researcher will use in-depth and semi-structured interviews with infertile couples individually and in pairs. Guiding questions will be designed for in-depth interviews and used in semi-structured interviews. To collect data, voice recording, note-taking, and field notes will be used. This stage of the study will be conducted in comprehensive health centers and infertility centers in Isfahan.

#### Participants and setting

In the first phase of the study, participants will include Iranian infertile couples who underwent infertility treatment at Isfahan Fertility and Infertility Center. The couples will be selected using the purposeful sampling method with maximum diversity in terms of age, education levels, economic status, job, duration of infertility, type of infertility, cause of infertility, and level of adjustment with infertility. The inclusion criteria will include no history of mental disorders and at least 2 years of infertility.

#### Data collection

The participants will be selected using the purposeful sampling method. In order to invite the participants, the study objectives will be explained, and the interview time and setting will be determined. Participants’ details will be recorded before the interview. Moreover, the fertility adjustment scale will be completed by participants to ensure sampling with maximum diversity in terms of the adjustment with infertility.

In a face-to-face meeting, data will be collected through in-depth interviews, voice recordings, and field notes of the observations. Couples who are willing will participate in the interview as a pair. Considering the psychological conditions of the participants and their readiness to be interviewed, the interview may be postponed or stopped and resumed another day.

The interview will be unstructured to allow the discovery of new ideas and will be continued using semi-structured interviews. An interview will be developed containing a list of questions to be asked during the interview with the participants. To further deepen the interview and gain richer data, some exploratory questions such as “Could you explain this through more examples?” will be used. Data collection will be continued until data saturation.

#### Data management and analysis

These data will be inductively analyzed using qualitative content analysis and interpretative phenomenological analysis introduced by Smith et al. [19]. The process of the interpretative phenomenological analysis will include reading, re-reading, noting, finding patterns across the data, and interpreting the data. Each interview and the related observations will be considered as a research unit. The recorded interviews will be listened to and transcribed. Themes from all transcriptions will be juxtaposed and clustered together across the cases. The subordinate themes will be collated and extracted.

To evaluate the validity and reliability of the data, credibility, dependability, conformability, and transferability standards will be used as the scientific accuracy criteria. In order for credibility, the member checking technique will be used to verify the trustworthiness of the data and codes. In order to ensure dependability, initial codes and examples of the categories, themes, and items extracted from the texts of the interviews for each category will be provided to an external observer. To ensure confirmability, the text of a number of the interviews and extracted codes and categories will be provided to research colleagues and three reproductive health and psychology experts, and they will be asked to evaluate the accuracy of the data coding process. In order to ensure the transferability of the findings, the participants’ statements will be presented as objectively as possible.

### Second phase: Delphi method

At this stage, an initial draft of couple-based strategies will be confirmed and validated. In the first round, to prepare an initial draft of couple-based coping strategies to deal with infertility as well as a questionnaire of open-ended items, firstly, the qualitative data will be analyzed; secondly, couple-based coping strategies to deal with infertility will be identified and extracted; thirdly, advanced reviews of related literature and document will be implemented. In order to improve, the initial draft will be sent (either by email or post) to 10 specialists, including psychologists and reproductive health specialists, to inquire about their opinion on the developed coping strategies.

In the second round, strategies modified in the first round will be ranked in a checklist using a Likert scale. In this round, moreover, coping strategies approved or disapproved by experts will be separated. In the checklist, there will also be a section for the participant experts to express their new ideas, correction, interpretation, and deletion; explain the strengths and weaknesses of the strategies; and elaborate on the reason for prioritization of coping strategies. The checklist will be sent to the experts to complete. The data will be reviewed and analyzed after receiving the completed checklists.

In the third round, the final checklist of couple-based coping strategies to deal with infertility will be prepared based on experts’ opinions in the second round and sent to the study experts to ask for their opinion. Furthermore, in this phase, the participants will be asked to review their answers, revise them if necessary, and present their reasons for any disagreement. The findings of both the qualitative study and the Delphi panel will be triangulated to design the field trial.

### Third phase: a randomized field trial study

#### Participants and setting

This parallel-group, double-blind, controlled, randomized field trial, superiority framework with an allocation ratio of 1:1 will be conducted on infertile couples who underwent infertility treatment in Isfahan Fertility and Infertility Center, Isfahan, Iran. Couples, at least one of whom suffers from mild to moderate depression, will be invited to participate in the quasi-experimental study. The inclusion criteria will include no history of severe mental disorders and no stressful event during the last 3 months. The exclusion criteria will be a stressful event or the onset of assisted reproductive treatment during the intervention and ovarian hyper-stimulation syndrome due to ovarian induction.

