#### Recruitment

Couple’s eligibility assessment and screening will be performed by the Ph.D. candidate in reproductive health. During the first interview, X infertile couples will be invited, and the levels of depression, anxiety, stress, and infertility adjustment will be evaluated using validated questionnaires. After determining the eligible couples, X couples will be randomly selected and invited by the researcher to participate in the study. The study objectives and the way of participating in the study will be explained to couples who accept the invitation.

The informed consent will be obtained from eligible couples by a legal advisor in the infertility center. The representative of the Ethics Committee of the Isfahan University of Medical Sciences will supervise all stages of the research and will decide to end the trial.

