#### Sampling and data collection

After determining the eligible couples, X couples will be randomly selected by the researcher. To randomly assign the couples to the intervention and control groups, X closed envelopes containing blue and green cards will be prepared. The couples will be referred to the midwife consultant and receive one of the envelopes and complete demographic characteristics.

The midwife and participants will be blinded to the study group. After random allocation, one researcher, who will not be involved in sampling and random allocation, will assign each group’s card color. Couples’ depression, anxiety, stress, and infertility adjustment levels will be evaluated using valid questionnaires 2 and 3 months after starting the intervention and compared between the groups (Table 1).

**Table 1 Tab1:** Schedule for data collection during the trial

Time point	Study period				
	Enrollment	Allocation	Post allocation		Closeout
	Pre-baseline	Baseline	Time 1	Time 2	
Enrollment					
Eligibility screen	X				
Informed consent	X				
Allocation		X			
Participant characteristics					
Demographics		X			
Infertility profile		X			
Interventions					
Couple-based coping strategies		X			
Solution-oriented counseling		X			
Outcomes assessment					
Depression			X	X	X
Anxiety			X	X	X
Stress			X	X	X
Infertility adjustment			X	X	X

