#### Intervention

The intervention will begin before starting medical treatment. The counselors will be MSc holders in psychological counseling. They will be trained in the developed couple-based coping strategies using face-to-face education and a role modeling approach.

For the intervention group, a counseling psychologist will be educated on the developed couple-based coping strategies based on the color chosen for one group (intervention group) and solution-oriented counseling for the other group (control group).

The number, duration, and intervals of the sessions for intervention and other educational intervention (control) groups will be set identically. It is estimated that the counseling program will be scheduled 3 to 5 times once or twice each week. The researchers will bear the intervention and transportation costs for both intervention and control groups. Participants should not participate in any other research during the intervention. The research is expected to proceed without any harm; however, in case of harm, the main researcher will be responsible for compensating for the reparable harm.

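### The trial is labelled double-blind, but counsellors must know the arm, the masked midwife neither treats nor measures, and every outcome is self-rated

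*Protocol article*

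**What the plan says.** Third phase, Participants and setting, gives the design label: "This parallel-group, double-blind, controlled, randomized field trial".

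Sampling and data collection says who is masked: "The midwife and participants will be blinded to the study group". It also gives the midwife's part: "The couples will be referred to the midwife consultant and receive one of the envelopes and complete demographic characteristics". Once couples have been allocated, a researcher who takes no part in sampling or allocation "will assign each group’s card color".

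Intervention describes the counsellors: "They will be trained in the developed couple-based coping strategies using face-to-face education and a role modeling approach". It adds that "a counseling psychologist will be educated on the developed couple-based coping strategies based on the color chosen for one group", with solution-oriented counselling for the other colour. The same section sets an identical number, length and spacing of sessions in the two arms, with an estimate of 3 to 5 sessions.

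Recruitment states: "The study objectives and the way of participating in the study will be explained to couples who accept the invitation". Data collection tools describes both instruments, DASS-21 and R-FAS, as self-report.

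**The concern.** In a counselling trial with subjective endpoints, a blinding label tells the reader how far to trust the comparison against two things. One is differential enthusiasm by those who deliver the programmes. The other is differential expectation in those who score the outcomes. Double-blind is normally read as protection against both.

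Here the second masked party is someone who hands over an envelope. Masking her helps conceal the allocation. It does nothing for delivery or measurement. If the label stands, a difference on depression, anxiety, stress or adjustment would be reported with more protection than the design gives it.

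The colour code raises a smaller matter. Its meaning is fixed only after allocation, and the article does not say that it is fixed by chance.

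**Working it through.** The article gives no figure on blinding to reproduce, so the check sets the sections against each other, party by party.

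1. **Counsellors.** Under Intervention they are trained in the new programme, and the content they give depends on card colour. Nobody can deliver a counselling programme without knowing which one it is. That they are unmasked follows necessarily from the text.

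2. **Midwife.** She is masked, but her described role is the envelope and the demographic form. No treatment or outcome role is given. Her masking protects allocation only.

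3. **Participants.** They are stated to be masked. They hear the objectives and then attend one of two programmes with different content. Against that, the control is active and the session format is matched, and nothing in the article says couples learn which programme is under test. The text supports masking to which programme is new. It cannot support masking to the content received.

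4. **Outcome assessors.** Both instruments are self-report, so the participants are the assessors. Protection of measurement therefore rests wholly on item 3. The researcher fills in missed data by telephone. The article does not say whether that person is masked; a fuller document may cover this, and it is not counted here.

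5. **Colour meaning.** Recruitment has the four outcome scores collected at screening, so baseline data exist before allocation. The meaning of the colours is assigned after allocation, with no stated random draw.

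**How far item 5 could matter.** This is a worst case, with inputs that are assumptions and not in the article. Let T be the standardised between-group difference in final score and B the same for baseline, both signed so that positive favours the new programme. Assume no true effect and correlation r between T and B. Suppose the colour with the better baseline were deliberately named the intervention.

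- Unadjusted final score: false superiority rate = 2·P(B > 0, T > 1.96); mean shift = r·√(2/π) standard errors.
- Full baseline adjustment: the adjusted difference is independent of B, so the rate stays at 2.5%.
- ANCOVA used only if baseline differs at p < 0.05 (my threshold; the article gives none): rate = 2·P(0 < B < 1.96, T > 1.96) + 0.05 × 0.025.
- Change from baseline, with equal variances: its correlation with B is −√((1 − r)/2), put into the first formula in place of r.

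| r | Unadjusted | Shift (SE) | Full ANCOVA | ANCOVA if baseline p < 0.05 | Change score |
|---|---|---|---|---|---|
| 0.3 | 3.8% | 0.24 | 2.5% | 3.5% | 0.2% |
| 0.5 | 4.5% | 0.40 | 2.5% | 3.7% | 0.5% |
| 0.7 | 4.9% | 0.56 | 2.5% | 3.4% | 0.8% |

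**The case against.** The strongest reply is that the article does name two masked parties, and that participant masking is credible. The comparator is another counselling programme with the same session format, and explaining the objectives is an ordinary part of consent that does not reveal an arm. If couples do not know which programme is new, their self-ratings come from masked raters.

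Most of this stands. A reader might infer that participants are unmasked because they hear the objectives and rate themselves. The documents do not support that. They state that participants are masked, and no section says couples are told which programme is experimental. Unmasking is possible but not shown. What the reply does not answer is that the counsellors know the arm and that the midwife's masking protects neither delivery nor measurement.

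On the colours, a reader might infer that assignment after allocation raises the false superiority rate from 2.5% to between 3.8% and 4.9%. The documents do not support that as an expected size. It needs a deliberate choice on baseline scores by a researcher whom the article keeps out of sampling and allocation, followed by an unadjusted analysis. Data management and analysis plans ANCOVA on enrolment scores when the groups differ at enrolment, which lowers or removes the inflation. On change scores, which Outcomes also lists, the same choice would work against the new programme.

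It is also fair that late assignment conceals: whoever issues a card cannot know an arm that has not yet been named. An earlier draw must preserve this.

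**Conclusion.** The point holds as a mismatch between the label and the design described. Counsellors are unmasked with certainty, the masked midwife has no described treatment or outcome role, and all outcomes are self-rated. The design supports participants who are not told which programme is new, aided by the matched active control, plus a masked allocator.

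The size of any resulting bias cannot be computed from the article. The conclusion rests on the text alone and assumes only that a counsellor knows the content he or she delivers. The colour assignment is secondary: no random draw is stated and one is easily added, but there is no sign of misuse.

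**What to change.** - Replace double-blind under Participants and setting with a plain account: participants not told which programme is the new one, midwife masked, counsellors not masked, outcomes self-rated.
- Describe the two programmes to couples in neutral terms when the objectives are explained.
- Have the independent researcher set the colour meaning by a random draw, sealed before the first envelope is issued and kept from the midwife and participants. This replaces assignment after allocation and keeps the concealment.
- As an optional check, ask each couple at 3 months which programme they believe is the new one.

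The cost is some wording, one sealed draw and, if wanted, one questionnaire item. Sample size, treatment and visit schedule are unaffected. The downside is a less favourable design label.

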#### Outcomes

The outcome will be the mean score of depression, anxiety, stress, and infertility adjustment and the magnitude of their change on enrollment and 3 months after starting the intervention in couples in the intervention group compared with those in another educational intervention (as the control group).

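### Two exclusion criteria can act only after allocation; unless the couples they catch stay in follow-up and analysis, the comparison risks selection bias

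*Protocol article*

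**What the plan says.** The protocol article, third phase, Participants and setting, describes a "randomized field trial, superiority framework with an allocation ratio of 1:1". The inclusion criteria there are "no history of severe mental disorders and no stressful event during the last 3 months". The next sentence gives the exclusion criteria: "The exclusion criteria will be a stressful event or the onset of assisted reproductive treatment during the intervention". It then adds ovarian hyperstimulation syndrome, without a time window.

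Under Sampling and data collection, eligible couples see the midwife consultant, where they "receive one of the envelopes and complete demographic characteristics". Table 1 places allocation at baseline. Under Intervention, counselling is then delivered according to card colour, and "The intervention will begin before starting medical treatment". Questionnaires are due "2 and 3 months after starting the intervention and compared between the groups". The Outcomes section says: "The outcome will be the mean score of depression, anxiety, stress, and infertility adjustment", together with the change in these scores.

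Three other places touch on couples who go off course. Data collection tools provides telephone calls to encourage couples who stop or depart from the counselling, and telephone completion of missed data. Data management and analysis fills missing values by last value carried forward. Sample size allows for loss. None of them mentions couples who meet an exclusion criterion after allocation.

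**The concern.** Randomisation makes the two arms comparable as allocated. That protection carries over to the analysis only if what decides who is counted does not depend on what happens after allocation. Here two of the stated exclusion criteria are events that happen after allocation.

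A stressful event is close to the outcomes themselves, three of which are depression, anxiety and stress. The arms receive different kinds of counselling, so what couples disclose as stressful, or when they begin assisted reproduction, could differ by arm. If couples are dropped at different rates, or if those dropped differ from those kept by a different amount in each arm, the retained groups can differ with no treatment effect at all. The arm that loses more high-scoring partners would look better.

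There is also a practical loss. Questionnaires that are not sent to an excluded couple cannot be recovered later by any choice of analysis set.

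**Working it through.** **Order of events**

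1. Stressful events before entry are already covered by the inclusion criterion with its 3-month look-back. The exclusion criterion would be redundant unless it refers to later events, and its wording says that it does.
2. The envelope is given at baseline and counselling follows by card colour. An event during counselling is therefore an event after allocation.
3. Counselling begins before medical treatment, so assisted reproduction can start inside the counselling period.
4. The telephone calls, the imputation rule and the allowance for loss do not say that an excluded couple keeps receiving questionnaires or is analysed.

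The article states no exclusion rate, standard deviation or sample size, so it has no figure to reproduce. Everything below is illustration with assumed inputs and a true treatment effect of zero.

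**Illustration in DASS points**

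Let p be the share excluded in an arm, and d the amount by which excluded partners score worse than retained partners. The mean of the whole arm equals the retained mean plus d × p, so exclusion shifts the retained mean by −d × p. With the same d in both arms, the spurious difference is d × (p₁ − p₂). Take d = 3 (assumed).

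| Excluded, arm 1 vs arm 2 | Shift, arm 1 | Shift, arm 2 | Spurious difference |
|---|---|---|---|
| 15% vs 15% | −0.45 | −0.45 | 0 |
| 10% vs 5% | −0.30 | −0.15 | 0.15 |
| 25% vs 15% | −0.75 | −0.45 | 0.30 |
| 30% vs 15% | −0.90 | −0.45 | 0.45 |

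Equal rates are not enough by themselves. With 15% excluded in both arms but d = 3 in one and d = 1 in the other (assumed), the shifts are −0.45 and −0.15, again a difference of 0.30.

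The definition of d matters. If the 3 points were the gap from the mean of the whole arm, the shift would be −d × p/(1 − p). Then 25% vs 15% gives 1.00 − 0.53 = 0.47, and 30% vs 15% gives 1.29 − 0.53 = 0.76. The table uses the gap from retained partners, which is the more natural reading of scoring worse.

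**Illustration in standard deviations**

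Let r be the assumed correlation between the tendency to be excluded and the outcome. The mean of those kept is −r × φ(z)/(1 − p), where z is the standard normal quantile at 1 − p and φ is the standard normal density. The type I error is two-sided at a nominal 5%, with 100 independent scores randomised per arm (assumed).

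| Excluded | Bias, r = 0.3 to 0.5 | Type I error |
|---|---|---|
| 10% vs 10% | 0 | 5.0% |
| 10% vs 5% | 0.03 to 0.04 SD | 5.4% to 6.0% |
| 20% vs 10% | 0.05 to 0.08 SD | 6.1% to 8.0% |
| 30% vs 10% | 0.09 to 0.15 SD | 8.8% to 15.7% |

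With r = 0 the bias is zero at every pair of rates. A simulation agreed with the formula to within 0.01 SD.

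**Precision**

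Dropping couples costs precision even without bias. At an average of 20% excluded, the standard error rises by a factor of 1/√0.8 = 1.118, about 12%, compared with analysing everyone.

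**The case against.** The strongest reply is that the article never says in so many words that these couples leave follow-up or analysis. The wording might mean only that counselling stops. The article is condensed, and an analysis plan that is not shown could define the analysis set. The stated aims of complete follow-up, telephone completion of missed data and imputation suggest a wish to keep couples.

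Part of this stands: removal from the analysis is the ordinary meaning of an exclusion criterion, not an explicit statement. It does not dispose of the point. Exclusion criteria belong in the protocol, and this one is stated. An analysis plan that kept these couples would have to override it, and could not recover questionnaires that were never sent.

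The size of the problem is also open to challenge, and here more stands:

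- A reader might infer that starting assisted reproduction is imminent and common. The article says only that counselling comes first and gives no interval or rate. The window is three to five sessions at one or two a week, roughly one to five weeks, so rates may be well below those in the tables.
- A reader might infer that exclusion must differ by arm. The control is also counselling, with the same number, length and spacing of sessions, and participants are described as blinded. Both features make large differences less likely, though the content of the counselling still differs.
- A reader might infer that the most distressed couples are the ones removed. That is plausible for stressful events, but nothing in the article supports it for starting treatment.
- A start of treatment that is already scheduled could be known at screening. The criterion as written, however, turns on the start itself, not on a plan to start.

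**Conclusion.** The point holds as a risk to validity. As written, two exclusion criteria act on randomised couples, one of them is closely tied to the outcomes, and no text keeps those couples in follow-up or analysis.

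A reader might go further and conclude that couples will certainly be removed and that the comparison has lost the protection of randomisation. The article does not support that. Removal is not spelled out, and equal, non-differential exclusion gives no bias.

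The size cannot be derived from the article. Under the assumed 3-point gap from retained partners, the spurious difference is 0.15 points at 10% vs 5%, 0.30 at 25% vs 15% and 0.45 at 30% vs 15%. Without a standard deviation in the article, these values cannot be weighed against a meaningful effect. The wording should be settled before recruitment because the missing follow-up could not be restored afterwards.

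**What to change.** - Limit the exclusion criteria to facts known before the envelope is opened, and remove those that turn on events during counselling.
- Record stressful events, the start of assisted reproduction and ovarian hyperstimulation after allocation as intercurrent events, and report them by arm.
- Continue the planned 2- and 3-month questionnaires for these couples.
- Analyse all randomised couples in the arm to which they were allocated.
- Show the analysis without the affected couples only as a sensitivity analysis.

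The cost is a wording amendment and sending questionnaires that are already planned to couples who would otherwise be dropped; the telephone follow-up is already foreseen. The downside is that the estimate includes couples with such events and may be slightly diluted. Whether counselling continues after such an event is a separate matter for the clinical team.
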